# Using traditional rhyme (folk song) as a tool for oral hygiene promotion (UTRATOHP) among children in rural communities in Nigeria: A protocol for a randomised controlled trial

**DOI:** 10.1371/journal.pone.0280856

**Published:** 2023-06-02

## Abstract

**Background:**

Most oral diseases are caused by poor oral hygiene, and with adequate oral hygiene measures, they are easily preventable. The use of folk songs to deliver oral health education may likely hold a huge potential for success and an increased likelihood of acceptability and sustainability among school children. Therefore, an investigation into the effectiveness of methods that would be culturally appropriate and sustainable, such as folk songs, is essential.

**Aim:**

To determine the effect of traditional rhyme (folk song) as a tool for oral hygiene education among children in rural communities in Nigeria.

**Materials and methods:**

This is a school-based, assessor-blinded, two-arm cluster-randomised controlled trial that will assess the effectiveness of oral hygiene messages delivered through traditional rhyme (folk song) on children’s oral hygiene knowledge, attitude, practices, and oral hygiene status in two rural communities (Igboora and Idere) in Nigeria. The study will involve a minimum of 424 participants (aged 7–9 years) selected from eight primary schools using the cluster sampling technique. Four schools will be randomised into the test group to receive oral hygiene messages through folk songs, and the participants will sing the song for two weeks. The other four schools will be assigned to the control group, and the participants will receive the usual oral health talk on oral hygiene practices by a dentist. The participants’ oral hygiene knowledge, attitude, practice and status will be assessed at baseline, immediate, six, and twelve-month post-intervention. A modified World Health Organization (WHO) Children’s oral health survey questionnaire will be utilised for data collection. Oral examinations will be conducted to assess the participants’ dental caries experience and oral hygiene status using the dmft/DMFT and simplified oral hygiene indices, respectively.

**Discussion:**

Folk songs are popular means of conveying messages in Nigeria, and using them to deliver oral health messages may be an effective, acceptable, and sustainable method among children. This study will provide empirical information about this innovative intervention to guide policy development, dental public health practice, and future studies.

**Trial registration:**

Pan African Clinical Trial Registry-PACTR202010863892797 (October 2020).

## Introduction

Oral diseases remain major public health problems with a substantial personal, social, and economic burden [1]. Worldwide, the prevalence of oral diseases like dental caries and periodontal diseases is high as they affect most people in high- middle- and low-income countries (HICs and LMICs) [1]. It is estimated that 2.4 billion people suffer from dental caries of permanent teeth, and 486 million children suffer from dental caries of primary teeth [2]. The global increase in the prevalence of dental caries [3, 4] highlights the need for primary prevention programmes, especially in LMICs, including sub-Saharan Africa, which has the highest burden of untreated dental caries [1, 5]. Dental caries are painful, negatively impact the quality of life, and may result in tooth loss and systemic infection that can lead to death in its advanced stage [6]. The treatment options for dental caries are costly, averaging 5% of the total health expenditure and 20% of out-of-pocket expenditure in developed countries [7]. In most developing countries, investment in oral health is low, and if treatment were available, the costs of dental caries in children alone would exceed the total healthcare budget [8]. Similarly, periodontal diseases contribute significantly to the global burden of oral disease, leading to pain, bleeding, bad breath, tooth loss, and adverse systemic illnesses [9]. Most epidemiological studies have observed significant relationships between socio-economic status and periodontal disease [10–13]. Low income and low education contribute to poor periodontal disease status [10–12]. There is an unequal burden of oral diseases affecting those in the rural areas more than those in the urban communities [13], and more among those living in slums than non-slum areas [12].

Most oral diseases like dental caries and periodontal problems are preventable [9]. Dental caries is one of the most common oral diseases that negatively impact the oral health-related quality of life of those affected [14]. While it can affect people over their life course [15], the risk is higher among children [15]. Given the cost of treatment and devastating effect on the quality of life, prevention of dental and other oral problems must be prioritised. The common preventive measures include maintaining good oral hygiene, eating a balanced diet with low refined-carbohydrate content, and regularly visiting the dental office for a check-up, early detection, and treatment of emerging oral problems [16, 17].

It is advocated that oral health education programs are instituted among the people living in Africa and the Middle East, including those in rural and underserved communities, to instil good hygiene practices among them [13]. There is an urgent need for educational interventions among Nigerian children with several reports stating that many of them have poor oral hygiene knowledge and behaviour [18–22]. These interventions are particularly useful when they are carried out among children who are just forming behaviours that affect their health [23, 24]. Helping children develop the habit of brushing twice daily and maintaining good oral hygiene is key to a lifetime of healthy smiles. Thus, exploring the roles of innovative methods such as oral hygiene songs, particularly folk songs with an inherent cultural motif at developing and probably sustaining good oral hygiene habits among children becomes pertinent.

Educational interventions that are based on behavioural models, including the Information-Motivation-Bavioural Skill (IMB) model, are usually more successful than those without it [25]. The IMB model, a theoretical framework developed by Fisher and others [26], presupposes that the successful adoption of health behaviour is contingent on three key factors: adequate knowledge about the behavior, motivation (positive personal attitudes and social support) to engage in the behavior, and the possession of self-efficacy and appropriate skills to undertake the behaviour [26]. The IMB model is a widely recognized approach used in modifying health behaviours among different population groups, including children and adolescents [26–28].

Songs help in conveying messages to people, help them retain those messages, motivate them into action [29], and it has been used to successfully improve public health knowledge and behaviours [30]. The use of songs is an effective approach to educating children and adolescents about proper oral health practices [31]. Through music, children can learn and retain information about oral hygiene in an enjoyable manner, thereby forming healthy habits that last a lifetime [32]. Toothbrushing songs that are set to familiar tunes can be particularly effective, as they make learning about oral health engaging and accessible [31, 32]. To enhance the effectiveness of such songs, traditional melodies can be adapted to include lyrics that reinforce key oral hygiene concepts. Parents, guardians, and schoolteachers can all leverage the power of music to teach children the importance of brushing and maintaining good oral hygiene. Additionally, using songs as a reminder to brush regularly is a fun and engaging activity that can be shared between parents, guardians, and their children daily [33]. Although using folk songs to deliver oral health messages holds much promise, there is a lack of empirical information about its use among children in Nigeria. Hence, this study aims to determine the effect of traditional rhyme (folk song) as a tool for oral hygiene education among children in rural communities in Nigeria.

## Materials and methods

### Study design

The research is designed to be a cluster-randomised, assessor-blinded, controlled trial with two study groups—intervention and control. The randomised control design was adopted to provide a high level of evidence for the study. The IMB model will form the framework for the study (Fig 1).

**Fig 1 pone.0280856.g001:**
[figure not shown]
Theoretical framework for the study.

### Study location and site

The planned study sites are Igboora and Idere, two rural communities in Ibarapa Central Local Government Areas of Oyo State, Southwestern Nigeria, which are about seven kilometres apart. Farming and petty trading are common in the two communities, and Yoruba is the predominant tribe and language [34]. There are 80 basic schools (primary schools) in the two communities [35]. Most primary schools have classes from Primary one (Pry 1) to Primary six (Pry 6), while some end at Pry 5 [36]. Generally, most classes have five arms (A–E), and preliminary investigation shows that each class arm has an average of 25 pupils. The official entry age into primary school i.e. Pry 1 class is six years, while they exit Pry 6 and start secondary school at age 12 years [36, 37]. However, because the rule is not strictly upheld, some schools enroll children into the Pry 1 class at ages four and five years [36, 37]. Since the usual age of entry into primary school ranges between four to six years, those in Pry 4 are usually between 7–9 years old [37].

### Study population

The study participants would comprise Pry 4 pupils from primary schools located in the two rural communities (Igboora and Idere) in Oyo State, Nigeria. The choice of the Primary 4 class pupils is for the following reasons: the pupils’ ages range from seven to nine years, and they usually would have started supervised but unassisted oral hygiene practices like tooth brushing [38, 39]. The age group (7–9 years) also has a higher likelihood of providing better responses during the interviews than younger people from the lower classes [40]. Moreover, pupils in the Pry 4 class are more likely to remain in their various schools through the proposed study period, unlike those in higher classes (Pry 5 and Pry 6) who may be nursing the idea of writing the secondary school qualifying examinations (common entrance examinations) and leaving their various schools while this study is still ongoing.

### Eligibility criteria

#### Inclusion criteria

Healthy children with parental consent will be included in the study.

#### Exclusion criteria

Primary schools not registered with the Oyo State Government will be excluded from the study. Pupils who do not understand the Yoruba language will also be excluded because the intervention (folk song) is in the Yoruba language.

### Sample size determination

The sample size for this study was determined using the formula for comparing two proportions [41]. The primary outcome is oral hygiene status. The prevalence (P_1_ = 38.4%) of children who had good oral hygiene from a previous study in Nigeria [42], was used for sample size calculation. An estimated 50% increase in the proportion of participants with good oral hygiene following the intervention (P_2_ = 57.6%) was used in calculating the minimum sample size. Other considerations were statistical power of 80%, a significance level of 5%, a non-response rate of 10%, an attrition rate of 20%, and an estimated design effect of 1.5. A minimum of 212 participants will be recruited per study group, making 424 for the two groups.

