The participants in the control group will be exposed to conventional health education on adequate oral hygiene practices conducted by the dentist [50]. Similar to the test group, there will be three intervention sessions. The first session will last for 40 minutes and will involve expert-led health talks and question and answer with the participants. The second and third sessions will also take place after two and four weeks, respectively. The follow-up sessions will involve revising the oral health messages with the participants, lasting for about 20 minutes each. None of the participants (control and test groups) will be denied access to oral health talks that they may be exposed to away from school.

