#### Data analysis plan

Baseline data would be compared among the two study groups based on their sociodemographic characteristics and the baseline value of the outcome variables (oral hygiene status, DMFT/dmft, caries status, knowledge, attitude, and practice). Subsequently, the intervention effects on the outcome variables will be assessed over the study period (baseline, immediate, 6 months, and 12 months assessments). The effectiveness would also be compared between groups (test vs control) over the 12 months (baseline, 6 months, and 12-month assessment). An intention-to-treat analysis will be employed for this study [51]. A participant will remain in the originally assigned group, notwithstanding what happens during the study, such as deviation from the study protocol or loss to follow-up. The data obtained at the previous assessment will be recorded for those lost to follow up in the subsequent assessments. The level of statistical significance for all tests will be set at p < 0.05.

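### The stated 80% power holds only if dentist-led education leaves the control arm at the survey rate, and neither the aim nor the analysis plan ties the song's effect to that comparator

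*Protocol article*

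**What the plan says.** **Aim.** The Abstract gives the aim as "To determine the effect of traditional rhyme (folk song) as a tool for oral hygiene education among children in rural communities in Nigeria". The Introduction closes with the same aim. Neither names a comparator.

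**Sample size determination.** The formula is the one for comparing two proportions. P1 is 38.4%, described as the prevalence "of children who had good oral hygiene from a previous study in Nigeria". P2 is 57.6%, obtained from "An estimated 50% increase in the proportion of participants with good oral hygiene following the intervention". With 80% power, 5% significance, 10% non-response, 20% attrition and a design effect of 1.5, the article arrives at 212 pupils per group, 424 in all.

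**Intervention and control groups.** On the comparator: "The participants in the control group will be exposed to conventional health education on adequate oral hygiene practices conducted by the dentist". It adds: "Similar to the test group, there will be three intervention sessions". The control sessions last 40, about 20 and about 20 minutes, with the second and third at two and four weeks. The song sessions have the same number, length and timing. The test arm additionally sings every school morning for a month under a teacher's supervision.

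**Data analysis plan.** Intervention effects on the outcomes are to be assessed across the study period from baseline to 12 months. Effectiveness is then also to be compared between test and control. No non-inferiority or equivalence margin appears, and there is no arm without education.

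**The concern.** Two parts of the article do not fit together. The target difference is a rise over a prevalence measured in an earlier study, and it is used as the difference between two arms that are both taught oral hygiene. If the dentist's sessions improve oral hygiene at all and the song arm ends at the stated 57.6%, the true contrast is smaller than the 19.2 points on which the trial is powered.

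The second part is interpretation. The randomised contrast can show only whether the song does better than dentist-led education. An aim that speaks of the song's effect without a comparator, next to a planned assessment of change over time, leaves room for two errors:

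- Improvement within the song arm, which has no untreated comparison, could be reported as the effect of the song.
- A non-significant difference between arms could be read as showing that the song does nothing, or that it is as good as the dentist's talk. The design supports neither.

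The article wants its results to guide policy. For that purpose, better than talks, as good as talks, and better than nothing are different conclusions.

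**Working it through.** **Inputs.** From Sample size determination: p1 = 0.384, p2 = 0.384 × 1.5 = 0.576, 80% power, 5% significance, 10% non-response, 20% attrition, design effect 1.5, 212 per group. The article does not say whether the test is one- or two-sided; two-sided is assumed.

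**Step 1: reproduce the stated figure.** With the unpooled two-proportion formula:

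n = (1.96 + 0.8416)² × [0.384 × 0.616 + 0.576 × 0.424] / 0.192² = 102.4 per arm.

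Inflated: 102.4 × 1.5 / (0.9 × 0.8) = 213, against 212 stated. The arithmetic is sound; the question is the control rate.

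**Step 2: effective size per arm.** 212 × 0.9 × 0.8 / 1.5 = 101.8.

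**Step 3: power at other control rates.** SE = √{[pc(1 − pc) + ps(1 − ps)] / 101.8}, and power = Φ(d/SE − 1.96), where pc is the control rate, ps the song rate and d = ps − pc. The article gives no expected rate after dentist-led education, so every pc above 38.4% is an assumption. The last column replaces the normal reference with a non-central t on 8 − 2 = 6 degrees of freedom, with noncentrality d/SE, because only eight schools are randomised.

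| Control | Song | d | SE | d/SE | Power, normal | Power, t on 6 df |
|---|---|---|---|---|---|---|
| 38.4% | 57.6% | 0.192 | 0.0687 | 2.79 | 80% | 65% |
| 42% | 57.6% | 0.156 | 0.0692 | 2.25 | 62% | 47% |
| 45% | 57.6% | 0.126 | 0.0695 | 1.81 | 44% | 33% |
| 48% | 57.6% | 0.096 | 0.0697 | 1.38 | 28% | 21% |
| 50% | 57.6% | 0.076 | 0.0697 | 1.09 | 19% | 15% |

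A pooled-variance formula gives 79%, 61%, 44%, 28% and 19% in place of the normal column, so the choice of formula hardly matters.

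**Step 4: the opposite scenario.** Keep the 50% relative rise and apply it to a higher control rate. For 45% against 67.5%, d/SE = 0.225 / 0.0677 = 3.32 and power is 91% (90% pooled). For 50% against 75%, d/SE = 0.250 / 0.0656 = 3.81 and power is 97% (96% pooled). The song arm must then go well beyond the stated 57.6%.

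**Step 5: aim, comparator and analysis side by side.** The aim has no comparator. The only randomised contrast is song against dentist-led education. The analysis plan lists effects over time first and the between-group comparison as an addition. Nothing in the article says which of the two supports a claim of effectiveness.

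**The case against.** An active or usual-care comparator is a legitimate choice, and the article discloses it in both the Abstract and the methods. Any trial of that kind estimates the difference from its comparator; that is not an error. This stands.

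A reader might infer that the aim and target effect are set against no education. The documents do not support this: the aim is silent on the comparator, and the sample-size section never mentions untaught children. The earlier study is not shown. Because the Abstract calls the control talk the usual one, 38.4% might even have been meant as the rate under usual education. If so, the article does not say it, and the control rate still lacks a stated basis.

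The arms are matched in their sessions only. Daily supervised singing for a month is a reason to expect a gain over the talks, and Step 4 shows that power rises if that gain is large enough. So the direction of the power change depends on assumptions, and it would be wrong to conclude that a null result is likely.

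Finally, the article nowhere says that a null will be read as equivalence or as no effect, and detailed rules of interpretation can be left to an analysis plan that is not shown. That limits the point to a risk: a null could be misread, not that it would be. The risk still has a footing in the article's own text, which places assessment over time beside the randomised comparison and does not rank them.

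**Conclusion.** The concern holds in a limited form. The sample-size arithmetic is right, but its 80% power depends on an unstated condition: that three dentist-led sessions do not raise the control arm above the 38.4% survey rate while the song arm reaches 57.6%. With the song arm held there, a control gain of 3.6 points (to 42%) lowers power to about 62%, and one of 6.6 points (to 45%) to about 44%. If the 50% relative rise holds over a 45% control rate, power is about 90%. These are illustrations on assumed control rates. The normal-theory figures are optimistic with eight schools.

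On interpretation, the design identifies only the song's advantage over dentist-led education. It cannot establish the song's effect against nothing, or equal effectiveness, and the present wording of the aim and analysis plan does not guard against either claim. The documents do not support the stronger readings that the comparator is wrong, that the aim was set against no education, or that the trial is bound to end in a misread null.

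**What to change.** - **Aim (Abstract and Introduction):** name dentist-led oral hygiene education as the comparator and state a superiority hypothesis for delivery by folk song.
- **Data analysis plan:** make the between-arm difference with its confidence interval the only basis for a claim of effectiveness, and treat change within an arm as descriptive. State that a non-significant result is evidence neither of equal effectiveness nor of no effect.
- **Sample size determination:** state that 38.4% against 57.6% assumes no control-arm gain over the survey rate. Give illustrative power for higher control rates: with the song at 57.6%, about 62%, 44%, 28% and 19% at control rates of 42%, 45%, 48% and 50%; and about 90% if the 50% relative rise is kept over 45%. Label these as assumptions, and as optimistic with eight schools.

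The sample size, schools, sessions and assessments stay as they are. The cost is wording, and a stated power that looks less favourable.

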### Sampling technique, recruitment, and randomisation

A two-stage cluster sampling technique will be employed for this study.

In the first stage, four schools from each of the two communities will be selected from the list of schools that would be obtained from the Ministry of Education, Oyo State, using the simple random sampling technique, making eight schools in total. In the second stage, an average of 55 participants will be selected from each selected school’s Pry 4 class arm using a proportionate sampling technique.

The schools will be the randomisation unit. The eight selected schools in the two communities (Igboora and Idere) will be randomised into either the test or the control group using the block randomisation method, aided by computer-generated numbers [43]. A website [44], for generating randomisation lists will be utilised for this purpose. Before using the website, the eight selected schools would have been assigned code numbers from “01” to “08”. The needed parameters will then be entered into the website and it would automatically generate the allocation sequence with the code numbers (schools) already assigned to the two study groups (Group A-Test; Group B-Control). Subsequently, the result of the randomization would be downloaded for future reference. The whole process of randomization will be conducted by an expert who is not familiar with the details of the study.

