#### Independent variables

The independent variables would include the participants’ study group, sociodemographic characteristics (age, gender, neighbourhood), and school-related characteristics (school type, class level).

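### No stratum for community is stated when the eight schools are allocated, so balance of the two communities between arms is not guaranteed

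*Protocol article*

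**What the plan says.** All places are in the Protocol article.

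- **Sampling technique, recruitment, and randomisation.** Sampling is structured by community: "four schools from each of the two communities will be selected". Then "The schools will be the randomisation unit", and the eight schools "will be randomised into either the test or the control group using the block randomisation method, aided by computer-generated numbers". Before that step, "the eight selected schools would have been assigned code numbers from “01” to “08". Finally, "The needed parameters will then be entered into the website", and the site returns the allocation sequence. The section does not say what those parameters are, what defines a block, or whether the codes follow community.
- **Abstract, Materials and methods.** The overall ratio is fixed at 4:4: "Four schools will be randomised into the test group" and "The other four schools will be assigned to the control group".
- **Discussion.** Distance between schools will be considered at selection, and neighbouring schools may not end up in opposing arms. The randomisation section does not mention this rule.
- **Independent variables.** The list includes "sociodemographic characteristics (age, gender, neighbourhood". The article describes no adjusted model.

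**The concern.** Community shapes the sample but is not said to shape the allocation. A block on a single list of eight secures 4:4 overall; it does not secure 2:2 within Igboora and within Idere. With only eight randomised units, chance imbalance on a two-level factor is common.

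At stake is the comparison of song with health talk in the one trial that will be run. If oral hygiene differs between the communities for any reason, an uneven split carries part of that difference into the unadjusted contrast. If each arm is one whole community, no model can separate arm from community.

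**Working it through.** **Inputs.** Eight schools, four per community, four per arm (randomisation section and Abstract). Planned difference 57.6 − 38.4 = 19.2 percentage points with good oral hygiene (Sample size determination). The plan states no probability of imbalance, so there is no figure of its own to reproduce on this point.

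**1. One unrestricted list.** The number of 4:4 splits is C(8,4) = 70. The number with k schools of one community in the test arm is C(4,k) × C(4,4−k), which is 1, 16, 36, 16, 1 for k = 0 to 4.

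- 2:2 in each community: 36/70 = 51.4%
- 3:1: 32/70 = 45.7%
- 4:0: 2/70 = 2.9%
- Unbalanced in total: 34/70 = 48.6%

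**2. Other readings of the block settings.**

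| Code order | Block size | Unbalanced | Fully confounded |
|---|---|---|---|
| By community | 4 or 2 | 0% | 0% |
| Random | 2, 4 or 8 | 48.6% | 2.9% |
| Alternating | 4 | 18/36 = 50% | 2/36 = 5.6% |
| Alternating | 2 | 10/16 = 62.5% | 2/16 = 12.5% |

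**3. The distance rule on one list of eight.** Distances between schools are not given, so these patterns are assumed, with close schools taken to lie in the same community. Both fully confounded splits then remain admissible while other splits drop out.

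| Schools that must share an arm | Admissible splits | Unbalanced | Fully confounded |
|---|---|---|---|
| One pair | 30 | 60% | 2/30 = 6.7% |
| One pair in each community | 14 | 71% | 2/14 = 14% |
| Two pairs in each community | 6 | 33% | 2/6 = 33% |
| All four of one community | 2 | 100% | 100% |

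Total imbalance can rise or fall; full confounding rises in every pattern shown.

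**4. Effect on the estimate.** Let the communities differ by d points in percent good, with schools of equal size. After a 3:1 split the community shares are 75% and 25%, so the unadjusted difference moves by (0.75 − 0.25) × d = d/2. After a 4:0 split it moves by d. The documents give no d. For an assumed 10 points (range 5 to 15):

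- 3:1 shifts by 5 points (2.5 to 7.5), which is 26% (13% to 39%) of 19.2
- 4:0 shifts by 10 points (5 to 15), which is 52% (26% to 78%) of 19.2

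**5. What adjustment can do.** After a 3:1 split the arm–community correlation is (3×3 − 1×1)/16 = 0.5. The variance inflation is 1/(1 − 0.25) = 1.33, and √1.33 = 1.15, so the standard error is about 15% larger than with 2:2. After 4:0 the correlation is 1 and the effect cannot be estimated with community in the model.

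**6. Allocation within community.** C(4,2) × C(4,2) = 36 allocations, all 2:2. Imbalance and full confounding are both 0%.

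**The case against.** A reader might infer that the allocation is definitely unstratified and that 49% and 3% are this trial's risks. The text does not support that. It names block randomisation and leaves the settings open; codes sorted by community with blocks of four or two would balance community exactly. The percentages also need all 70 splits to be equally likely, which the distance rule may prevent. They are conditional figures.

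A reader might also infer that the communities are known to differ. Nothing shows this. Study location and site describes both as rural, in the same local government area, about seven kilometres apart, with the same common occupations and main language. The Discussion says the investigators' clinics serve both. Nor does anything say that neighbourhood, as listed among the independent variables, means Igboora versus Idere.

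Unstratified blocked randomisation is valid, and over repeated allocations it is unbiased. A 3:1 split is repairable at modest cost. Block size is also a detail that an article may leave to the full protocol.

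All of this stands, and it limits the size of the point. It does not remove it. The section describes coding, website, download and operator, and at no step does it secure balance by community. Under the published procedure, balance would depend on how code order and block size happen to combine. The operator is described as unfamiliar with the study's details and cannot be relied on to supply the stratum.

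A last objection is that forcing 2:2 puts opposing arms in the same community and invites spillover. But a single unrestricted list already does so in 68 of 70 splits, so stratifying adds little. What remains is that 2:2 must be compatible with the distance rule.

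**Conclusion.** The point holds as a design improvement that should be made. As described, the allocation does not guarantee that the communities are balanced between arms. Under one unrestricted 4:4 list, or codes in random order, the chance of imbalance is 48.6%, of which 2.9% is full confounding. Across the other block settings the text allows, imbalance ranges from 0% to 62.5%. If the distance rule binds within a community, full confounding becomes more likely, by an amount that cannot be fixed without the distances.

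The consequence depends on a community difference that the documents do not report. Imbalance after a 3:1 split is a loss of precision if community is adjusted for; only a 4:0 split is beyond repair.

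**What to change.** - Randomise within community: one block of four Igboora schools and one of four Idere schools, each with two test and two control. State this in the randomisation section.
- Include community as a factor in the between-arm comparison.
- Reconcile the randomisation section with the distance rule in the Discussion. The cleaner way is to apply the rule when schools are selected, so that any 2:2 split is admissible. Otherwise treat a close pair as one unit within its community. Three or more mutually close schools in one community cannot be split 2:2 under the rule.

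**Cost.** Two list generations in place of one. A school-level analysis loses one degree of freedom (8 − 2 = 6 becomes 8 − 3 = 5). At most 36 allocations remain instead of 70. The plan names no permutation test, but if one were used, the smallest two-sided p-value would be 2/36 = 0.056 rather than 2/70 = 0.029, so it could not reach the plan's 0.05 threshold. A model-based or school-level t analysis does not have this limit. A tied pair leaves only 2 allocations in its community (2 × 6 = 12 in all), which is a further reason to apply the distance rule at selection. Doing so may restrict which schools can be drawn.
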